### Study outcomes

The main study variable is the improvement on the ventricular function measured angiographicaly as described below. This efficacy outcome is measured as the changes on the LVEF evaluated by a cardiologist blinded to the patients’ clinical follow-up. With this objective, patients undergo cardiac catheterization in two study timepoints: on the date of the intracoronary infusion of either experimental treatment or placebo (visit 3) and at month 6 (visit 5) after infusion.

Secondary efficacy outcomes include clinical evaluation and NYHA functional grade, BNP or N-terminal fragment of pro-brain natriuretic peptide (NT-proBNP) blood levels, echocardiogram, exercise testing according to Naughton protocol, without oxygen consumption as well as biological parameters of the BMMNC product that may predict a good response (cellularity, chemotaxis and stem cell markers: CD133+, CD34+, CD34+/CD177+,CD34+/CD38-, CD34+/CXCR4+, CD34+/DR-, VEGFR2+, CD90+, CD105+, CD73+, CD14-, CD45-).

Study variables regarding safety are measured as appropriate during follow-up visits: adverse events (AEs) and serious adverse events (SAEs), causally related with study interventions or procedures (including marked changes of vital signs, abnormalities physical examinations and out of range laboratory test results). Additionally, the protocol emphasizes the identification of specific adverse events: major cardiac events or MACEs (defined as cardiac death, major arrhythmia, inclusion in heart transplant waiting list, cardiac resynchronization therapy interventions and hospital admission due to clinically relevant adverse cardiac events), symptoms and signs of arrhythmia, evidence of myocardial harm and tumoral biomarkers abnormalities.

The study design, evaluations and assessment timeline for all variables is illustrated in Fig. 1. After product infusion, all patients are followed-up for 24 months according to protocol by interventional or clinical cardiologists at the participating hospitals. Protocol programmed visits are structured in 9 time-points that include two pre-infusion visits (screening and randomization), BMMNC/placebo infusion day, and 6 post-infusion follow-up evaluation time-points according to a decreasing frequency: 24 h, 3 months, 6 months, 12 months, 18 months and 24 months. Trial investigators must ensure that essential clinical, analytical and exploratory data is registered in the study’s Case Report Form (CRF).

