### Echocardiographic measurement of ventricular function

Echocardiography is used as a secondary endpoint for the purpose of comparison with published trials, as well as to provide additional non-invasive time points of LVEF evaluation. LV function will be measured with echocardiography at baseline (visit 1) as well as 6 (visit 5), 12 (visit 6), 18 (visit 7) and 24 (visit 8) months after infusion, using standardized imaging protocols to calculate ejection fraction using the Simpson’s rule. Although a discrete positive correlation has been described among LV angiography and echocardiography estimates [39], LVEF measurements by various techniques are generally not interchangeable [40]. However, LVEF changes trends measured with LV angiography will be compared with those obtained using echocardiography, and the intra-subject correlation among both LVEF estimates will be analyzed in order to stablish a correlation that may help explain the long and short-term effects of BMMNC.

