LVEF improvement is the main study variable, and it will be evaluated angiographically by an expert angiographer blinded to treatment allocation and patient’s progression. Although this technique is not the gold standard for LVEF estimation, the approach will reduce inter-observer variability and provide more accurate, repeatable results, avoiding some of the limitations of echocardiographic estimates. Cardiovascular Magnetic Resonance (CMR) was not a feasible option in the context of this study due to the high frequency of devices (Cardiac Resynchronization Therapy Defibrillator or CRT-D) in this population that interfere with CMR scans results. Also, not all participating sites had equivalent CMR techniques, which may have provided LVEF estimates based on non-comparable images, leading to increased variability of results. Consequently, the main limitation of the present trial design is its comparability across studies that measure LVEF using magnetic resonance imaging.

In order to reduce the risks of left ventricular angiography, only two assessment points are stablished throughout follow-up (at baseline and 6 months after treatment). Also, the risk of contrast-induced acute kidney injury is minimized by the exclusion of patients with serum creatinine higher than 2,5 mg/dL. However, as the moment of highest benefit (if any) after cell infusion is still unclear, complementary non-invasive measurements of LVEF using 2D echocardiography are set out at baseline, as well as at months 3, 6, 12, 18 and 24 after treatment. Although both estimates will not be interchangeable, a correlation may be stablished that will allow for drawing conclusions about the long and short-term effects of BMMNC.

In conclusion, the results of the present trial are expected to envision a new therapeutic alternative for the treatment of idiopathic DC. Current pharmacological treatments aim to improve blood flow and prevent further damage to the heart, but they are not curative. Stem cell therapy constitutes a promising alternative to palliative care, restoring cardiac structure and function. Once the safety and efficacy of this advanced therapy product is established in humans, the final goal will be to confirm these observations in future phase II and/or phase III clinical trials involving a larger number of subjects.

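### A correlation between angiographic and echo LVEF cannot carry conclusions on short- and long-term BMMNC effects; the between-arm echo comparison can

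*Protocol article*

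**What the plan says.** The section on echocardiographic measurement makes echo LVEF a secondary endpoint. It cautions that "LVEF measurements by various techniques are generally not interchangeable". It then plans two things: a comparison of the trends in LVEF change by the two methods, and a correlation ("the intra-subject correlation among both LVEF estimates will be analyzed"). The stated purpose there is soft: "in order to stablish a correlation that may help explain the long and short-term effects of BMMNC". The Discussion repeats that the estimates are not interchangeable, but goes further on purpose: "a correlation may be stablished that will allow for drawing conclusions about the long and short-term effects of BMMNC".

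The two schedules differ. The Study outcomes section places the angiograms "on the date of the intracoronary infusion of either experimental treatment or placebo (visit 3) and at month 6 (visit 5) after infusion", and the Discussion confirms that "only two assessment points are stablished throughout follow-up". For echo, the methods text reads "LV function will be measured with echocardiography at baseline (visit 1) as well as 6 (visit 5), 12 (visit 6), 18 (visit 7) and 24" months. The Discussion also lists a month 3 echo.

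For quantitative efficacy variables, the section on data management and statistical analysis names only before-after tests within patients (paired t-test or Wilcoxon). The article names no between-arm analysis of echo LVEF.

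**The concern.** The Discussion gives the correlation an inferential job: it is to allow conclusions about what BMMNC does early and late. A correlation shows whether two measurements rise and fall together. It does not show whether they give the same size of change, and it says nothing about treatment unless the arms are compared. Here it can be estimated only from the infusion-day and month 6 angiograms, while the late period of interest is months 12 to 24.

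At stake is how the long-term results are read. A respectable r could lend late echo trends an angiographic meaning that the trial cannot verify. Meanwhile echo is collected in both randomised arms and supports a direct answer on its own scale.

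**Working it through.** **The plan's own figures.** The article gives no number for the correlation analysis. The only related figures are in the sample size section: SD 10, baseline-to-final correlation 0.5, difference 9 units, two-sided alpha 0.05, power 80%, 10% loss, 2:1 allocation.
- SD of change = 10 × √(2 × (1 − 0.5)) = 10.
- Smaller arm: 1.5 × (10 × (1.96 + 0.84) / 9)² ≈ 14.5, rounded up to 15; larger arm 30.
- With 10% loss: 15/0.9 = 16.7, so 17; 30/0.9 = 33.3, so 34.

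The stated 17 and 34 reproduce. Nothing below changes them.

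**1. How much information there is.** Each patient has at most two angiogram-echo pairs. The sensible estimate pools patients after removing each patient's own mean. With two pairs per patient, that is in effect a correlation of one angiographic change with one echo change per patient. By Fisher's z, with half-width 1.96/√(N − 3), r = 0.5 has a 95% interval of 0.24 to 0.69 with 45 patients and 0.26 to 0.68 with 51.

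**2. What it cannot see.** Let echo change = 0.5 × angiographic change in every patient. Then r = 1 exactly, yet a true 9-point difference would appear as 4.5 points. Adding a constant to every echo value also leaves r unchanged.

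**3. Where it cannot be checked.**

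| Time | Angiogram | Echo |
|---|---|---|
| Baseline | visit 3 | visit 1 |
| Month 3 | none | Discussion only |
| Month 6 | visit 5 | visit 5 |
| Months 12, 18, 24 | none | visits 6, 7, 8 |

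Only the month 6 pair shares a visit. The baseline pair is split between screening and infusion, and the interval is not given, so any drift between those visits enters both changes unequally. After month 6 the relation is pure extrapolation.

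**4. Scale of disagreement (illustration only).** Assume SD 10 for both methods and no mean bias. The SD of the difference between methods is √(2 × 100 × (1 − r)), and the 95% limits are 1.96 times that.
- r = 0.8: √40 = 6.32, limits ±12.4 points.
- r = 0.9: √20 = 4.47, limits ±8.8 points.

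These limits are for one patient. The same scatter on the mean of 34 patients at r = 0.8 is 12.4/√34 ≈ ±2.1 points.

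**5. From levels to changes.** Take r = 0.8 between methods at a visit and 0.5 over time within a method, so each change has variance 2 × (100 − 50) = 100.
- Method errors independent over time: true-score variance 80, true-score covariance over time 50. Covariance of changes = 2 × (80 − 50) = 60, so r between changes = 0.6.
- Method errors fully persistent within a patient: true-score variance 80, persistent method variance 20, true-score covariance over time 30 (30 + 20 = 50). Covariance of changes = 2 × (80 − 30) = 100, so r = 1.0.

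A level correlation of 0.8 is therefore compatible with anything from about 0.6 to 1.0 between changes, depending on something the article does not state.

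**The case against.** The defence is substantial. The article disclaims interchangeability in both places and plans to compare change trends as well as to correlate. The methods section claims only that the correlation may help explain effects, and the stronger sentence is conditional Discussion text, not an analysis rule. Echo LVEF is a secondary endpoint in its own right. A condensed article may also leave the choice of agreement statistic to the full protocol or analysis plan. All of this limits the weight. What remains is that the Discussion names a use that the correlation cannot serve, whichever statistic is chosen.

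Four stronger readings are tempting and are not supported:
- A reader might infer that an intra-subject correlation on two points can only be +1 or −1, so the analysis is meaningless. That holds for a separate r in each patient. The pooled within-subject correlation can be estimated, and because it removes patient means, the spread of baseline LVEF does not drive it.
- A reader might set ±12.4 or ±8.8 against the 9-point target. Those are single-patient limits; the target is a difference between group means.
- A reader might conclude that r = 0.8 between levels means only 0.6 between changes. That is one end of a range.
- A reader might infer that late echo values will be converted to the angiographic scale, or that the correlation replaces the echo analysis. The article says neither.

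**Conclusion.** The point holds, with minor weight. The Discussion, and more softly the echocardiography section, attach conclusions about short- and long-term BMMNC effects to a correlation that rests on about one change per patient, cannot detect constant or proportional bias, uses a baseline pair from different visits, and cannot be verified after month 6. These statements follow from the schedule and from what a correlation is; they need no assumed values. The limits of agreement and the 0.6 to 1.0 range are illustrations that assume an SD of 10 for echo and, for the limits, no mean bias. The analysis is secondary. The primary endpoint and the sample size of 51 are untouched.

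**What to change.** 1. Base conclusions on short- and long-term effects on the randomised between-arm comparison of echo LVEF at each visit, adjusted for baseline echo LVEF, for example in a mixed model for repeated measures.
2. Handle separately any echo data collected after a control patient receives the cryopreserved cells through compassionate use, because from then on the arms no longer contrast cells with placebo. The article allows this after a positive second interim analysis; its trial design section speaks of finalized patients, so the number of affected visits may be small.
3. Keep the method comparison descriptive. Alongside any correlation, report bias with 95% limits of agreement at baseline and month 6, and the slope of angiographic change on echo change. Note that the baseline pair comes from two visits. Do not extend the relation past month 6.
4. Amend the Discussion sentence to match, and reconcile the two echo schedules on month 3.

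The cost is wording in the analysis section and one sentence of the Discussion. No new measurements or patients are needed.

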### BMMNCs biological characterization

To analyze biological predictive factors of response to treatment [27], aliquots of the cellular suspension infused to experimental group patient are obtained for the following purposes:
Automatic cell count for evaluation of total infused cellularity.Immune phenotype characterization: BMMNCs aliquots (1–5 × 10^5^ cells) are stained with fluorochrome-conjugated monoclonal antibodies (FITC, PE and APC) against human cell surface markers CD34, CD133, VEGFR2, CXCR4, CD90, CD38, CD117, HLA-DR, CD45, CD105, CD73, CD14. After incubation for 15 min in darkness, BMMNCs are washed with PBS and centrifuged for 5 min at 1800 rpm. The cell pellet is then resuspended in PBS, stained with Propidium Iodide (Miltenyi Biotec) to measure cellular viability as analyzed with MACSQuant cytometer (using MACSQuantify software for quantitative measurements).Cell chemotactic ability: BMMNCs migration in response to VEGF (R&D Systems, Inc., Minneapolis) and SDF-1 (R&D Systems, Inc., Minneapolis) was assessed using 24-well culture plates and 8 μm pore size inserts (BD Biosciences, Erembodegem, Belgium). A dose of 5 × 10^4^ cells is placed in the system using serum free media RPMI-1640 (BioWhittaker® LONZA, Verviers, Belgium) and 100 ng/ml of VEGF, 100 ng/ml SDF-1 or nothing (control well). After 24 h of incubation at 37 °C, cell migration is quantified using a Neubauer chamber.

### Concomitant medication

All patients must be treated with optimized conventional cardiac insufficiency medication for at least 6 months before the inclusion date and throughout follow-up, involving the use of angiotensin-converting-enzyme inhibitors, angiotensin II receptor blockers, beta-blockers, aldosterone antagonists or other diuretic drugs, potassium supplements etc. Additionally, those patients with ejection fraction lower than 30% may also receive digoxin. Treatment should be optimized following medical judgement according to patient’s symptoms/tolerance (NYHA functional class) and/or BNP levels.

Although the combination of cell therapy with G-CSF has been proven efficacious in previous reports [30], this trial has been designed to evaluate solely the effect of BMMNCs, without any stimulating factors that may interfere with the findings.

However, no other therapy to improve the ventricular function in a mechanical way, as resynchronisation therapy or cardiac transplantation, will be used during follow-up. However, non-responders to a previously implanted defibrillator can be included. In the pilot study performed by our group an inverse correlation was found among basal high-density lipoprotein (HDL) serum levels and LVEF improvement (r = − 0,41, *p* = 0,03) [32]. Consequently, patients with a lower baseline values of HDL could attain a higher improvement in LVEF. On this account, patients included in the study should not be treated with statins affecting HDL blood levels (rosuvastatin, pitavastatin and atorvastatin) 2 months prior to inclusion, as well as throughout follow-up. A wash-out period of two months is established for patients under any prohibited medication prior the inclusion in the study.

### Sample size calculation

A sample size calculation was performed based on the clinical trial study already completed by our group [32]. In this study, a mean increase in ejection fraction of 9.4 ± 9.9% was observed. At the end of the follow-up, mean values of LVEF were 38% among responders, and 27% among non-responders. The sample size calculation was done using GRANMO (v7.12) for paired or repeated measures in two groups. Accepting an alpha risk of 0.05 and a beta risk of 0.2 in a two-sided contrast, 17 subjects are required in the first group and 34 in the second one to detect a difference equal to or greater than 9 units. It is assumed a common standard deviation of 10 and a correlation coefficient between the initial and final measurement of 0.5. A loss to follow-up rate of 10% has been estimated. However, an interim analysis has been planned in order to re-calculate trial sample size based on the mean increase in ejection fraction observed in the first 20 patients that complete a 6 months’ follow-up period.

### Randomisation and blinding process

Randomisation is centrally performed by the sponsor, stratified by age (> or ≤ 45 years old) in a 2:1 block randomisation allocation BMMNCs or placebo. As sample size is small and both planned interim analysis may require a balanced distribution of the subjects within both study groups, block randomization is applied. Randomization list was computer generated by the Sponsor, and allocation is kept concealed for the research teams recruiting patients.

Investigators and patients (as well as clinical monitors) are blind to the treatment assigned. In the case of SAE, when the patients’ management could be improved by the knowledge of the blinded treatment assigned, the principal investigator may request the sponsor formal permission for subject unblinding. Additionally, specific unblinding of patients allocated to the control group may be authorized by the sponsor to allow for the treatment through compassionate use with their own previously cryopreserved BMMNCs.

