Different experimental studies in animal models of DC have shown improvements in ejection fraction and decreases in the ventricular volumes after cell therapy [12–21]. These benefits have also been established in clinical studies aimed at analysing the safety and efficacy of bone marrow-derived progenitor cells in patients with DC [22–31]. In 2006, the ABCD trial [26] described for the first time in humans improvements in the NYHA functional class, a decrease in end-diastolic volume and an average improvement of 5.4% in the ejection fraction in 24 patients with DC treated with intracoronary BM-derived cells. A long term follow-up of this trial showed that the functional benefits achieved were maintained without late adverse effects [25]. Similarly, Fischer-Rasokat et al. [23] observed in 33 patients with DC that intracoronary administration of BM-derived cells appears to be associated with improvements in cardiac contractile and microvascular function in patients with DC (ref). More recently, these results have been confirmed by the REGENERATE-DCM clinical trial [30], in which a 5.37% increase in left ventricular ejection fraction (LVEF) was observed at 3 months after treatment with autologous BM-derived cells combined with peripheral granulocyte colony-stimulating factor (G-CSF). Next to these previous experiences, our group has completed a one-year Phase II Clinical Trial (NCT00629096, EudraCT 2007–003088-36) to evaluate the safety and efficacy of intracoronary infusion of autologous BMMNCs in 27 patients with DC [32]. In this study, an improvement in the New York Heart Association (NYHA) functional class and a reduction of brain natriuretic peptide (BNP) plasma levels were observed without any adverse effect. In addition, a significant decrease in ventricular volumes along with a mean increase in the ejection fraction of 9% in 20 out of the 27 patients was observed at month 6. These changes suggest a favourable effect of cell therapy on ventricular remodelling, which may explain the decrease (or even disappearance) of the degree of mitral regurgitation observed in some patients. However, the gain in ejection fraction after cell therapy varied greatly between patients, ranging from − 9% to + 34%, being this gain greater in patients with a baseline ejection fraction < 25%. The clinical benefit of cell therapy was stable 5 years after infusion, with 69% survival rate and 43% of patients free of major events, staying within a NYHA functional class of I-II [33]. Interestingly, younger patients seemed to show the highest long term response to cell-based therapy in terms of LVEF improvement. However, contradictory reports have been published which show no improvements in ejection fraction, NYHA functional class, or exercise test outcomes after intracoronary infusion of autologous BMMNCs in patients with DC [29]. However these findings should be interpreted with caution as, despite apparent similarities, important methodological differences exist among published reports: BMMNCs dose, LVEF measuring technique, administration procedure, clinical description of eligible patients, subject follow-up length, use of G-CSF, technique of bone marrow cell harvesting etc. Ultimately, clinical studies using BM-derived cells in DC patients have shown only modest benefits [34–36]. We believe that the proposed clinical study may contribute with a new methodological perspective on search for cell therapy-based treatment alternatives in patients with DC. In summary, there is sufficient preliminary evidence to consider intracoronary injection of BMMNCs as a viable, safe and beneficial treatment in patients with DC. However, there is a need for larger, randomized, controlled studies to understand the biological mechanism of action of BMMNCs in the myocardium and the factors affecting clinical response to regenerative therapy with autologous BMMNCs in patients with DC.

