### Data management and statistical analysis

Clinical data is manually registered using a paper Case Report Form (CRF). CRF data is entered in the study database using an Electronic Data Capture (EDC) system. After double data entry, resolution of all inconsistencies, and coding by means of medical dictionaries, a final quality control process will be applied. In case of compliance, the database will be considered error free and will be frozen for the statistical analysis of the data. Sponsor and investigator will have access to the final trial dataset.

A descriptive analysis will be performed including all demographic variables collected, as well as baseline clinical data. Qualitative variables will be summarized using absolute frequencies and percentages, while quantitative variables will be described using the mean, median, standard deviation, maximum, minimum and number of observations.

The efficacy evaluation of quantitative parameters will be performed by comparing basal values (prior to the administration of the product) with those recorded in the follow-up visits, using the paired Student’s t-test (if the variable meets the normality requirements), or the Wilcoxon paired test for all other cases. For qualitative parameters, the Chi-square test will be used.

Two interim analyses will be performed during the study. The first one, to ensure the statistical power of the study, will be performed when the first 20 patients reach a minimum follow-up of 6 months, and will include a new sample size calculation based on these data. In the second one, the main variable under study will be analysed once 6-months of follow-up have been completed in all patients recruited. If the results are positive, patients randomised to the control group will be treated via compassionate-use basis with their own cryopreserved BMMNCs, as early mentioned. Per-protocol analysis (PPA) will be used for all efficacy assessments. All p-values and confidence intervals will be calculated and evaluated using a 95% two-sided confidence level.

Safety analysis is aimed at estimating the number and percentage of patients dropped out due to AEs, the number of patients who have experienced at least one AE, the most frequent AEs and the number of patients who experienced at least one SAE. The 95% confidence intervals will be also determined. Safety evaluation will be performed with intention-to-treat analysis.

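### The stated efficacy analysis is a paired before-after test: it names no between-arm test of LVEF, uses baseline LVEF only by subtraction and omits the age stratum, where one regression model would repair all three

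*Protocol article*

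**What the plan says.** - **Randomisation and blinding process:** "Randomisation is centrally performed by the sponsor, stratified by age", with the cut at 45 years, in blocks at 2:1.
- **Study outcomes** and **Angiographic measurement of ventricular function:** the primary endpoint is the change in angiographic LVEF from the infusion visit (visit 3) to month 6.
- **Sample size calculation:** a two-group repeated-measures calculation. The error rates are given by "Accepting an alpha risk of 0.05 and a beta risk of 0.2 in a two-sided contrast", the target is "to detect a difference equal to or greater than 9 units", and the variability is set by "It is assumed a common standard deviation of 10 and a correlation coefficient between the initial and final measurement of 0.5". The result is that "17 subjects are required in the first group and 34 in the second one", with 10% loss to follow-up.
- **Data management and statistical analysis:** for quantitative efficacy variables, basal values are compared "with those recorded in the follow-up visits, using the paired" t-test, or the Wilcoxon paired test where normality fails. No covariate, stratum term or between-arm test of LVEF is named.
- **Background and rationale:** in the group's earlier study the LVEF gain varied widely, "being this gain greater in patients with a baseline ejection fraction" below 25%. Younger patients seemed to have the best long-term response.

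**The concern.** Three parts of the design do not reach the analysis. The sample size rests on a difference between arms, but the named test looks at change within patients. A baseline value of the primary endpoint is obtained by catheterisation, but is used only by subtraction, which is inefficient when the correlation between the two measurements is 0.5. The randomisation is stratified by age, but the analysis does not reflect this.

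The Discussion describes recruitment as difficult and a larger trial as hard to manage, so precision available from data already collected is worth having. The month-6 analysis also informs whether control patients are offered their stored cells, so the comparison behind it should be one of BMMNC against placebo.

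Chance imbalance adds to the case. Randomisation is not stratified by LVEF, and with 15 and 30 patients the arms can differ at baseline by several points. A change-score comparison carries part of that difference into the estimate.

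**Working it through.** **Inputs** (Sample size calculation): two-sided alpha 0.05, power 80%, difference 9, SD 10 at both times, correlation r = 0.5, ratio 2:1, loss 10%.

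**1. Reproducing the plan's figure.**
- SD of change = 10 × √(2 × (1 − 0.5)) = 10.
- Smaller group = 1.5 × (10 × (1.960 + 0.842) / 9)² = 14.5, rounded up to 15; larger group 30.
- Loss: 15 / 0.9 = 16.7, so 17; 30 / 0.9 = 33.3, so 34.

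This gives 17 + 34 = 51 exactly. The calculation is therefore one for a between-arm comparison of change.

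**2. Variance with baseline as a covariate.**
- Change score: 2 × 100 × (1 − 0.5) = 100.
- Baseline-adjusted: 100 × (1 − 0.5²) = 75, a residual SD of 8.66.
- 100 / 75 = 1.33, the precision of about a third more patients.

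**3. Power at 9 points** (noncentral t; the adjusted model spends one degree of freedom on baseline and one on age stratum).

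| Evaluable (control/BMMNC) | Between-arm change score | Adjusted |
|---|---|---|
| 15/30 | 79.4% | 89.4% |
| 17/34 | 84.4% | 92.9% |

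With 15/30 the standard error is 10 × √(1/15 + 1/30) = 3.16 for change and 8.66 × √(1/15 + 1/30) = 2.74 adjusted. The difference detectable with 80% power falls from 9.06 to 7.86 points. A simulation of 20,000 trials gave 80.0% and 89.0%. An approximation that also charges for chance imbalance in both covariates gives 87.9% for the adjusted model.

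**4. Source of the gain.** At 15/30, adjustment for baseline alone gives 89.4%, and adding the age stratum leaves it at 89.4% if age explains no further variance. The documents give no age–LVEF correlation. If age is assumed to explain 0 to 10% of the residual variance, power is 89.4% to 92.2%.

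**5. Sensitivity to the correlation** (assumed range; SD 10 at both times; 15/30).

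| r | Adjusted / change variance = (1 + r)/2 | Power, change | Power, adjusted |
|---|---|---|---|
| 0.3 | 0.65 | 65.2% | 83.0% |
| 0.5 | 0.75 | 79.4% | 89.4% |
| 0.7 | 0.85 | 94.9% | 97.3% |

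**6. Sensitivity to unequal SDs** (assumed; final SD 10, r = 0.5).
- Baseline SD 8: change variance 64 + 100 − 2 × 0.5 × 8 × 10 = 84, against 75 (11% less).
- Baseline SD 7: 49 + 100 − 70 = 79, against 75 (5% less).

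**7. Chance imbalance.** With 15/30 the standard error of the baseline difference is 3.16 points. At a slope of 0.5, half of any imbalance passes into the change-score estimate: 1.6 points for an imbalance of one standard error and 3.2 for two.

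**8. What a paired test answers.** Assume no difference between arms, but a true improvement of 3 to 5 points in both. With an SD of change of 10, the paired test is significant with probability 36% to 75% among 30 patients and 19% to 44% among 15. Those results say nothing about BMMNC against placebo.

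**The case against.** The strongest reply is that covariates and stratum terms are commonly left to an analysis plan, which is not shown here, and that nothing in the design is invalid without them. Under randomisation an unadjusted between-arm comparison of change is unbiased, and the imbalance argument is conditional on the sample that happens to arise. Leaving out a balanced prognostic stratum usually makes the standard error too large, which is conservative. The plan's 51 patients give close to its stated 80% power without adjustment, and a sample-size recalculation is foreseen.

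Most of this stands as a limit on severity. It does not remove the point, because the article is not silent: it names a paired test for quantitative efficacy variables, and that test does not match the comparison it sized.

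A reader might infer more than the documents support:

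- **That baseline LVEF goes unused.** It is the subtracted member of each pair; what is missing is its use as a covariate.
- **That adjusting for age brings part of the power gain.** No figure in the article allows such a gain to be calculated.
- **That 79% is the power of the stated analysis.** It belongs to the between-arm change comparison assumed in the sample size, which the analysis section never names.
- **That the pilot establishes both covariates as prognostic.** Its observations come from treated patients. A larger gain at low baseline LVEF is compatible with regression to the mean, and the age finding is tentative and long-term.

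The equal-SD assumption also deserves weight. Eligibility limits LVEF on echocardiography, so the baseline SD may be below the final SD and the gain smaller.

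**Conclusion.** The concern holds as a mismatch between design and analysis that can be repaired almost without cost. The named test gives no between-arm comparison of LVEF, takes baseline only by subtraction and leaves out the stratum used in randomisation.

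Against the comparison the plan sized, baseline adjustment is worth about ten percentage points of power with 15/30 evaluable, or about eight to nine if nobody is lost. This rests on the plan's SD of 10 at both times and its correlation of 0.5. It shrinks with a higher correlation or a smaller baseline SD, and grows with a lower correlation. The case for the age term is agreement with the randomisation, not power.

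The documents do not show that the sample size is wrong or that an unadjusted between-arm comparison would be biased. This is a change that should be made, not a fatal fault.

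**What to change.** State the primary analysis as a linear regression of month-6 angiographic LVEF on treatment arm, visit-3 angiographic LVEF and age stratum (45 or under, over 45). Report the adjusted between-arm difference with its 95% confidence interval. Use the same form for the other quantitative efficacy outcomes, each with its own baseline. Paired within-arm results can stay as description.

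The cost is analysis wording and two degrees of freedom (41 in place of 43 with 45 evaluable patients). No new data are needed. The Data Availability statement reports that no datasets had yet been generated or analysed, so at the time of the article the model could still be fixed in advance.
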